### Statistical analysis

#### Primary endpoint

The primary endpoint will be analyzed on the intention-to-treat (ITT) population comprising all randomized patients in the arm where they were randomized. A per-protocol analysis will also be performed in patients without major deviation from the protocol. The evaluable population for treatment tolerance will be all patients who received at least one session of radiotherapy of any kind. PFS will be calculated from the date of randomization to the date of first evidence of a documented relapse, or until the date of death regardless of cause, or until the date of last news (data from patients who did not present the event at the time of the analysis will be censored). It will be estimated in each arm by the Kaplan-Meier method and compared between the two treatment arms by a Log-Rank test.

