## Methods and design

### Study design

The ETOILE trial is a multicenter open-label randomized parallel-group superiority trial comparing carbon ion therapy with standard radiotherapy, including a treatment by photons or protons. Patients will be enrolled in French reference centers for cancer treatment. Patients fulfilling the eligibility criteria will be randomized into two arms using a 1:1 ratio (experimental arm: carbon ion therapy; control arm: photon or proton therapy). Follow-up takes place 2 months and 6 months after the end of radiotherapy, then every 6 months during 5 years.

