### Study objectives and endpoints

The primary outcome is the progression-free survival (PFS) defined as the time from randomization to the first relapse or death, whatever the cause, or to the latest news date. Progression is defined according to RECIST v1.1 criteria [17] based on standard medical imaging (CT or MRI), and confirmed 6 months later. An independent committee unaware of the treatment group will validate all progressions.

Secondary outcomes include: the tolerance profile assessed using CTCAE-V4.02 grades; survival without locoregional progression; survival without metastases; overall survival; quality of life using the EQ-5D-3L. Associated health-economic and radiobiological studies are also planned.

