### Randomization

Randomization will be done using an Interactive Web Response Systems (IWRS). Stratification parameters include the center and the type of cancer (adenoid cystic carcinoma versus sarcoma and chordoma). As the trial design is open-label, no blinding of treatment assignment is possible.

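### Event-free patients are censored for PFS at last news, although progression is established on imaging; unscanned time counts as progression-free, and the hazard ratio is biased only if imaging stops unequally

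*Protocol article*

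**What the plan says.** The protocol article states the censoring rule twice.

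- Study objectives and endpoints defines PFS as "the time from randomization to the first relapse or death, whatever the cause, or to the latest news date".
- Statistical analysis, Primary endpoint, ends follow-up at relapse, at death, "or until the date of last news (data from patients who did not present the event"; those patients are censored at that date.

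Progression itself follows RECIST v1.1, "based on standard medical imaging (CT or MRI), and confirmed 6 months later". On review, the article says: "An independent committee unaware of the treatment group will validate all progressions". The visit schedule is common to both arms: "Follow-up takes place 2 months and 6 months after the end of radiotherapy, then every 6 months during 5 years". On blinding, the Randomization section says: "As the trial design is open-label, no blinding of treatment assignment is possible". The test is a log-rank comparison in all randomized patients. The Secondary endpoints section analyses overall survival by the same methods.

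**The concern.** Contact with a patient shows that the patient is alive, so last news is a sound censoring date for overall survival. It does not show the absence of progression when progression is read from scans. Suppose imaging stops at 2 years and the last contact is at 5 years. The stated rule then adds 3 years of progression-free time during which only death, or a relapse documented some other way, could count as an event.

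Two things follow. PFS is overstated in any arm where this occurs. If it occurs more in one arm, the log-rank comparison tilts towards that arm. The common schedule helps only while patients attend for scans. The blinded committee validates progressions that were found and cannot recover those that no scan looked for.

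**Working it through.** **Inputs from the protocol article.** 5-year PFS of 50% (control) and 70% (carbon), HR 0.515, 92 events, 90% power, 1:1 allocation, 250 patients, and the visit schedule. The alpha value is not printed; two-sided 0.05 is assumed.

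**The plan's own figures.** ln(0.70)/ln(0.50) = 0.5146, which matches 0.515. Power with 92 events is Φ(√92/2 × |ln 0.515| − 1.96) = Φ(4.796 × 0.664 − 1.96) = Φ(1.22), or 88.9%, close to the stated 90%. The sample size does not depend on this point.

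**Overstatement of 5-year PFS.** Assume exponential PFS, imaging stopping at a time uniform on 0 to 60 months, and contact continuing to 60 months. If no event at all is captured after imaging stops, a patient who stops at time u stays event-free with probability S(u) instead of S(60). The excess per stopping patient is mean S(u) − S(60), where mean S(u) = (1 − S(60)) / (−ln S(60)).

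| | Mean S(u) | S(60) | Difference | Per 10% stopping |
|---|---|---|---|---|
| Control | 0.5/0.6931 = 0.721 | 0.500 | 0.221 | 2.2 points |
| Carbon | 0.3/0.3567 = 0.841 | 0.700 | 0.141 | 1.4 points |

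These are upper values, because death remains an event after imaging stops. If 20% of first events are deaths (an assumption), that part of the hazard continues, and the excess is exp(−0.2x) × (1 − exp(−0.8x))/(0.8x) − S(60), with x = −ln S(60).

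- Control: 0.871 × 0.768 − 0.5 = 0.168, or 1.7 points per 10%.
- Carbon: 0.931 × 0.870 − 0.7 = 0.110, or 1.1 points per 10%.

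Deaths that follow an undetected progression reduce it further.

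**Effect on the hazard ratio with no true effect.** This was simulated with 125 patients per arm, 5-year PFS of 50% in both arms, scans about every 6 months, 20% of first events being deaths, a death hazard of 0.25 per year after progression, and stopping independent of progression. The nominal one-sided rate is 2.5%.

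| Imaging stopped, control vs carbon | HR, last-news censoring | False positives for carbon |
|---|---|---|
| Equal | 1.00 | nominal |
| 5% vs 20% | 0.95 | 4.0 to 4.3% |
| 10% vs 30% | 0.93 to 0.94 | 4.9 to 6.3% |

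**Two ways to censor at the last imaging, same two unequal scenarios.**

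- Survivors censored at last imaging, every later death counted: HR about 1.03 to 1.05. This over-corrects.
- Deaths more than 1 year after the last scan also censored at that scan: HR about 1.01.

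**A more extreme case.** Let imaging stop at 10% per year in carbon and never in control, so that 1 − exp(−0.5) = 39% of carbon patients stop over 5 years. Last-news censoring then gives HR 0.87 and 11.6% false positives. If both arms stop at 10% per year, the HR is 1.00, but PFS at 5.25 years reads 54% instead of 48% in each arm.

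**The case against.** The strongest reply is that the bias in the comparison is wholly conditional and the documents give little reason to expect its condition. A reader might infer from the open label and the treatment in Italy that carbon patients will be scanned less and the result will favour carbon. The article does not support that. Patients in both arms are enrolled in French centres and share one follow-up schedule. Carbon treatment lasts 4 weeks, and patients who cannot be followed for 5 years are excluded. Nothing says that carbon patients are followed abroad, so both the presence and the direction of any imbalance are unknown. A small imbalance also does little: with 5% against 10%, the HR stays at about 0.98 to 0.99. All of this stands and limits the size of the point.

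It is also too strong to say that progression could never be detected once scheduled imaging stops. The Primary endpoint section counts a documented relapse, and a patient with symptoms would plausibly be scanned. That too stands, and it is one more reason to read the percentage-point figures as upper values.

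A third reply is that missed-assessment rules belong in an analysis plan that is not shown. Their absence from the article is indeed no finding. But the censoring date is not absent. It is stated in both the endpoint definition and the analysis section, so it can be judged as written.

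**Conclusion.** The point holds in a limited form. The article fixes a censoring date that suits survival and applies it to an endpoint whose progression part is read from imaging. PFS is overstated wherever patients stop imaging but remain in contact, by at most about 2.2 points (control) and 1.4 points (carbon) per 10% of patients. The hazard ratio is affected only if stopping is unequal: about 0.95 with roughly 4% one-sided false positives at 5% against 20%, and about 0.93 to 0.94 with 5 to 6% at 10% against 30%. The bias can run either way, depending on which arm is scanned less.

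The stopping rates, the 20% share of deaths, the death hazard after progression, the alpha of 0.05 and the independence of stopping from progression are all assumptions; the documents give none of them. The point does not show that the trial's comparison will be biased. It shows that the stated rule leaves the comparison unprotected if imaging attendance differs.

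**What to change.** Change both Study objectives and endpoints and Statistical analysis, Primary endpoint, as follows.

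- Censor patients without documented progression or death at their last adequate tumour imaging, or at randomization if there is none after baseline.
- State a rule for events after missed assessments. One example is to censor at the last imaging any death that follows it by more than two scheduled visits (2 × 6 months, about 1 year). Without such a rule the change over-corrects, as the working shows.
- Keep last news as the censoring date for overall survival.
- Report PFS with last-news censoring as a sensitivity analysis.

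The cost is a few sentences, slightly less person-time, and a few deaths not counted in the primary PFS analysis. The date of each tumour assessment must be available for analysis; an imaging-based endpoint should supply it, but the article does not say so.

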### Sample size calculation

The study is calibrated to detect a treatment effect hazard ratio (HR) of 0.515 under the proportional hazards assumption, translating in an absolute improvement of the 5-year PFS rate of 20% in favor of the experimental arm (70% in the experimental arm vs 50% in the control arm).

A total of 92 events [East Software- Copyright@Cytel inc. 1994] notified in the study would have 90% power to show statistically significant PFS at a 2-sided alpha. Considering initial recruitment duration of 24 months and a 5-year follow-up for the last included patient, 108 patients per arm would be randomized in the study. To optimize the study and consider the possibility of withdrawal of consent and patients lost to follow-up, the recruitment objective was set at 250 patients.

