#### Interim analysis

An interim analysis is planned for effectiveness or futility. This analysis will be carried out when approximately 50% (46 events) of the final number of PFS events has been reached. The significance level at this interim analysis to establish the superiority or futility of experimental treatment over control with regard to PFS will be determined based on the observed number of events, using the O’Brien & Fleming boundaries as implemented by the Lan-DeMets alpha spending method (Lan and DeMets 1983) in order to control the overall Type I error rate.

Using planned enrollment rate, this analysis should be performed 42 months after first included patient. For example, if the number of events at the time of interim efficacy analysis is exactly 46, the bounds to use during this analysis according to Lan Demets rules will be *p* = 0.0031 and *p* = 0.8443 respectively to reject H0 and H1.

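### The primary log-rank test is stated without strata although randomisation is stratified by tumour type: valid, but conservative and less powerful than a stratified test if the types differ in prognosis

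*Protocol article*

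**What the plan says.** The Randomization section of the protocol article names two factors: "Stratification parameters include the center and the type of cancer (adenoid cystic carcinoma versus sarcoma and chordoma". Allocation is "randomized into two arms using a 1:1 ratio".

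The Primary endpoint section estimates PFS by Kaplan-Meier in each arm, to be "compared between the two treatment arms by a Log-Rank test". It names no strata and no covariates, and it does not use the word unstratified either. The Secondary endpoints section carries the same methods over to overall survival, and the Interim analysis section names no other test.

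The Sample size calculation section says: "The study is calibrated to detect a treatment effect hazard ratio (HR) of 0.515 under the proportional hazards assumption". It ties that figure to 5-year PFS of "70% in the experimental arm vs 50% in the control arm". These are rates for the whole trial; none is given by tumour type. The 92 events "notified in the study would have 90% power to show statistically significant PFS at a 2-sided alpha".

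**The concern.** Balancing the arms within tumour type removes the chance variation in outcome that would come from unequal case mix. A log-rank test without strata still counts that variation in its variance. If the types differ in prognosis, the variance is too large and the test rejects too seldom under the null. Pooling types with different baseline hazards also moves the overall hazard ratio towards 1 relative to the effect within each type. A test stratified on the same two-level factor avoids both effects.

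The trial rests on 92 events, so a few points of power are worth having when they need no extra patients. The sponsor thought tumour type important enough to balance on, which makes a difference in prognosis plausible. The article does not quantify one.

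**Working it through.** **Inputs from the article.** HR 0.515; 92 events; 108 patients per arm; 1:1 allocation; 24 months of recruitment; overall 5-year PFS of 50% and 70%.

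**Assumptions.** The two-sided level is not printed, and 0.05 is taken. The interim bound supports this: Lan-DeMets O'Brien-Fleming spending at half the information and two-sided 0.05 gives 0.00305, and the article prints 0.0031. The hazard ratio between tumour types and the case mix are not in the article, so ranges are shown.

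**The plan's own figures.**
- HR: ln 0.70 / ln 0.50 = 0.5146, which matches 0.515 and shows that it comes from the overall rates.
- Power (Schoenfeld): Φ(|ln 0.515| × √92 / 2 − 1.96) = Φ(0.6636 × 4.796 − 1.96) = Φ(1.22) = 88.9%, close to the stated 90%.

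**Reading A: HR 0.515 within each type, overall control 5-year PFS 50%.** Simulation of 216 patients balanced within type, exponential PFS, uniform accrual over 24 months, cut at the 92nd event, |Z| > 1.96, no interim look, 12,000 trials per row. Entries are unstratified / stratified; losses are taken before rounding.

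| Hazard ratio between types | Share in worse type | Type I error, % | Power, % | Loss, points |
|---|---|---|---|---|
| 1 | 50% | 5.0 / 5.0 | 87.9 / 87.7 | none |
| 1 | 70% | 5.1 / 5.0 | 87.6 / 87.6 | none |
| 2 | 50% | 4.6 / 5.2 | 86.3 / 87.8 | 1.5 |
| 2 | 70% | 4.7 / 5.0 | 86.8 / 87.7 | 0.8 |
| 3 | 50% | 3.7 / 5.1 | 84.6 / 87.8 | 3.2 |
| 3 | 70% | 3.8 / 4.6 | 86.0 / 88.3 | 2.3 |
| 5 | 50% | 3.0 / 5.4 | 80.9 / 88.8 | 7.9 |
| 5 | 70% | 3.5 / 5.2 | 84.5 / 88.2 | 3.8 |

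The simulation standard error is about 0.3 points for power (√(0.88 × 0.12 / 12,000)) and 0.2 points for type I error (√(0.05 × 0.95 / 12,000)).

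Smaller runs (4,000 to 5,000 trials) with 30% or 50% in the worse type gave 84% against 88% at a ratio of 3, and 81–82% against 87–88% at a ratio of 4. Further runs gave unstratified type I error of 4.0–4.4%, 3.6–4.0% and 2.8–3.3% at ratios of 2, 3 and 4. Taken together, the loss is about 1 point at 2, 2 to 4 at 3, and 4 to 7 at 4. It is smaller when most patients are in the worse type.

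**Reading B: 50% versus 70% as overall rates, as the article gives them.** The within-type HR is solved so that the overall 5-year rates are 50% and 70%. Each cell gives the value for 50% / 70% in the worse type.

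| Hazard ratio between types | Implied within-type HR | Power unstratified, % | Power stratified, % |
|---|---|---|---|
| 1 | 0.515 / 0.515 | 88.0 / 87.6 | 88.0 / 87.6 |
| 2 | 0.504 / 0.507 | 88.7 / 88.4 | 90.1 / 89.0 |
| 3 | 0.489 / 0.499 | 89.4 / 89.5 | 92.0 / 91.1 |
| 5 | 0.462 / 0.487 | 91.2 / 89.6 | 95.5 / 92.3 |

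Here the unstratified test keeps its planned power and the stratified test exceeds it.

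**Why the readings differ.** Take a ratio of 4 and a 50:50 mix. Control 5-year PFS is then 72.45% and 27.55% (mean 50%). Raising each to the power 0.515 gives 84.7% and 51.5%, mean 68.1%. Reading A therefore tests a benefit of about 18 points, not 20, and part of the lower unstratified power in the first table comes from that smaller effect.

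**The case against.** The strongest objection is that the lack of strata is inferred from silence. The document is a condensed article, and whether a log-rank test is stratified is often settled in the full protocol or SAP, neither of which is shown. That stands as far as it goes: the article does not prove that the strata will be ignored. But it does name the primary test, and the test it names does not match the allocation scheme it describes. Stratifying by this factor is a specific improvement, not just a request for missing detail.

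It is also fair that an unstratified log-rank test is valid, is simple and matches the planned Kaplan-Meier curves. At a between-type ratio of 2 it costs only about a point. Nothing in the article shows that a split into adenoid cystic carcinoma and all other eligible tumours separates prognosis strongly.

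Three stronger readings are tempting, and the document supports none of them:
- *The trial falls short of its 90% power because of this test.* The article derives HR 0.515 from overall rates. On that reading the unstratified test keeps about 87 to 91% power, against a reproduced design figure of 88.9%.
- *The reported effect will be diluted relative to the HR the trial was sized for.* The article never states a within-type HR. The overall contrast is what an unstratified comparison addresses.
- *The false-positive rate is at risk.* The error runs the other way.

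**Conclusion.** The point holds as an efficiency gain forgone. Followed as written, the primary test is valid and conservative, and it is less powerful than a log-rank test stratified by tumour type whenever the types differ in prognosis. The power losses in points are for a common within-type HR of 0.515; on the overall-rates reading the stratified test is still ahead, by about 1 point at a ratio of 2 and 3 to 4 points at a ratio of 5. All of these sizes depend on assumed between-type hazard ratios and case mixes, a two-sided level of 0.05 and exponential PFS. The direction does not depend on the particular ratio, and with equal prognosis the two tests perform alike. The change is worth making, but the validity of the trial does not depend on it.

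**What to change.** Before any comparison by arm is seen, state in the Primary endpoint section and the SAP that:
- the primary log-rank test, at interim and final analysis, is stratified by tumour type (adenoid cystic carcinoma versus sarcoma and chordoma);
- centre is not a stratum in the test, because many small centre strata would be inefficient with 92 events;
- the hazard ratio comes from a Cox model stratified in the same way;
- the unstratified log-rank test is kept as a sensitivity analysis.

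If the SAP already stratifies the test, align the article's wording with it. The cost is a short addition to the text. It needs no more patients, data or events, and tumour type is already recorded at randomisation.

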### Patient selection

#### Inclusion/randomization criteria

Patients eligible for inclusion in this study have to meet all of the following criteria:age ≥ 18 yearsunresectable or inoperable cancer or a cancer with a macroscopically incomplete resection (R2)radioresistant cancers including: adenoid cystic carcinomas of the head and neck (excluding laryngeal and tracheal sites), soft tissue sarcomas, rhabdomyosarcoma of pleomorphic type only, retroperitoneal sarcomas providing technical feasibility, osteosarcomas of any localization and whatever the grade (Ewing’s sarcomas excluded), chondrosarcoma (excluding skull base) of WHO grade ≥ 2, chordomas of the axial skeleton and the pelvis (base of the skull excluded), and angiosarcomas (scalp angiosarcoma excluded).absence of epidermal invasion (a hypodermic invasion is accepted with cutaneous adherence but no permeation of the epidermis);largest dimension of the macroscopic volume (Gross Tumor Volume, GTV) < 20 cm;Performance Status ECOG ≤2 or Karnofsky Index ≥60;no severe comorbidities and life expectancy over 10 years;patient physically and mentally able to accept and receive cares far from their home;no ongoing pregnancy or risk of pregnancy for women of childbearing age;patient affiliated with a social security insurance;written informed consent to participate in the study.

Additional criteria are requested for randomization:validation of an indication for radiotherapy by a specialized local multidisciplinary tumor board (MTB) and, in the context of the indications of this study, validation of the indication and the feasibility for carbon ion therapy by the medical team of the National Center for Oncological Hadrontherapy (CNAO) in Pavia, Italy;possibility of offering carbon ion therapy within 2 months.

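### The primary PFS test is a valid but unadjusted log-rank; pre-specified adjustment for tumour size, resection status and histology could add about 0 to 6 points of power at little cost

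*Protocol article*

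**What the plan says.** The Primary endpoint section analyses PFS by intention to treat, estimates it by Kaplan-Meier, and has it "compared between the two treatment arms by a Log-Rank test". It names no stratum or covariate.

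The Randomization section stratifies by centre and by tumour type, the latter as "adenoid cystic carcinoma versus sarcoma and chordoma", so sarcoma and chordoma share one level. The Dose prescription section lists them as separate diseases.

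The Inclusion/randomization criteria require "largest dimension of the macroscopic volume (Gross Tumor Volume, GTV) < 20 cm". They admit both unresected and R2-resected disease, and name the eligible histologies, from angiosarcoma and osteosarcoma to chordoma. Checking eligibility therefore establishes size, resection status and histology for every patient.

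The Sample size calculation section states: "The study is calibrated to detect a treatment effect hazard ratio (HR) of 0.515 under the proportional hazards assumption". This corresponds to 5-year PFS of "70% in the experimental arm vs 50% in the control arm", with 92 events.

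**The concern.** Tumour size, resection status and the sarcoma/chordoma split enter neither the randomisation nor the primary test. If they predict PFS, a test adjusted for them has more power at the same number of events. Such power would be useful here, because more events require more patients or longer follow-up. Recruitment was planned for 24 months but, by the Status of the trial section, was still open about 51 months after the December 2017 start.

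This point is about covariates that are not randomisation factors. Whether the test should be stratified by the randomisation factors is a separate question.

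**Working it through.** **Inputs from the protocol article.** Allocation: patients are "randomized into two arms using a 1:1 ratio". HR 0.515; 92 events; 5-year PFS 50% vs 70%; 108 patients per arm, target 250; accrual 24 months; one interim look at 46 events.

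**Assumed.** Two-sided alpha of 0.05, because the Sample size calculation section prints no value. Also assumed are all prognostic effects and the shares of R2 and chordoma, none of which the documents give.

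**Step 1: the plan's own figures.**
- HR from the rates: ln 0.70 / ln 0.50 = 0.5146, matching 0.515.
- Schoenfeld power: |ln 0.515| × √92 / 2 − 1.960 = 0.6636 × 4.796 − 1.960 = 1.222, and Φ(1.222) = 88.9%. The plan says 92 events "notified in the study would have 90% power to show statistically significant PFS at a 2-sided alpha". This agrees to about one point. (Solving for exactly 90% gives 96 events.)
- Support for alpha 0.05: O'Brien-Fleming-type spending at half the information gives a one-sided 2 × [1 − Φ(2.241/√0.5)] = 0.001525, so two-sided p = 0.00305. Matching beta spending gives a futility p of 0.844. The Interim analysis section says "the bounds to use during this analysis according to Lan Demets rules will be" 0.0031 and 0.8443.

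The planned power is therefore that of the unadjusted test and never relied on adjustment.

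**Step 2: what adjustment would add.** Exponential PFS was simulated with the marginal 5-year rates held at 50% and 70%, analysed once at 92 events against 1.96.

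| Run | Prognostic effects | Plain log-rank | Adjusted | Change (points) |
|---|---|---|---|---|
| A | none | 88.5% | 88.0% | −0.5 |
| A | weak: 1.2 / 0.8 / 0.8 | 88.5% | 89.2% | +0.7 |
| A | moderate: 1.4 / 0.65 / 0.6 | 88.2% | 90.6% | +2.4 |
| A | strong: 1.7 / 0.5 / 0.45 | 87.9% | 93.7% | +5.8 |
| B | HR 1.0 per factor | 88.7% | 88.2% | about −0.5 |
| B | HR 1.25 per factor | 87.4% | 87.3% | about 0 |
| B | HR 1.5 per factor | 89.3% | 90.4% | about +1 |
| B | HR 2.0 per factor | 89.3% | 92.4% | about +3 |
| B | HR 2.5 per factor | 89.1% | 95.4% | about +6 |
| C | none | 88.8% | 88.3% | −0.5 |
| C | weak | 88.1% | 89.6% | +1.5 |
| C | moderate | 88.4% | 91.0% | +2.6 |
| C | strong | 88.7% | 93.6% | +4.9 |

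- Run A: 216 patients, Cox Wald test, HRs for size per SD / R2 (30%) / chordoma (35%), 5,000 trials per row.
- Run B: 250 patients, Cox Wald test, three binary factors at 50% each, 6,000 trials per row (Monte Carlo error about 0.4 points).
- Run C: 216 patients, covariate-adjusted log-rank. Its grades need not equal those of run A.

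**Step 3: what it would cost.**
- Type I error: A, 4.5–5.4% for both tests. B at per-factor HR 2, 5.0% plain and 5.3% Cox. C, 4.7–5.3% plain and 5.4–6.3% adjusted log-rank. Part of the gain in run C therefore reflects a slightly liberal test.
- Estimand: keeping the marginal 50% vs 70% in run B, the conditional HR moves from 0.515 to 0.483 at per-factor HR 2.0.
- Stratifying on all eight cells instead: 86.6% power with no prognostic effect, a loss of 88.7 − 86.6 = 2.1 points.

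**The case against.** The strongest reply is that nothing here is wrong. The unadjusted log-rank is valid, suits the proportional-hazards design and delivers essentially the power claimed. The article is a condensed account, and adjusted analyses may be set out in the full protocol or SAP. All of this stands. What remains is that the article does fix which test is primary, and a better one could be named from data already gathered.

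A reader might infer more than the documents support:
- *That the trial is giving up power for free.* Without prognostic strengths the loss cannot be asserted. The gain was negative or nil with no effect and at per-factor HR 1.25. Adjustment also has the costs shown in step 3.
- *That chance imbalance distorts the result.* With 35% chordoma (assumed) and 108 per arm, the SD of the difference in share is √(2 × 0.35 × 0.65 / 108) = 0.065, so a gap of 10 points or more arises in about 12% of trials. The error rate of the plain test already allows for this, as its simulated type I error of about 5% shows. Adjustment would sharpen the comparison; it does not repair a bias.

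Some limits of the simulations also stand. They used one analysis at 1.96, without the interim look. Runs A and B fitted three covariates and did not model adenoid cystic carcinoma separately, whereas three-level histology makes four covariate parameters. Pooling all sarcomas still leaves part of the heterogeneity unaddressed.

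**Conclusion.** The point holds as a cheap efficiency improvement, not as an error in the plan. The stated primary test uses none of three baseline variables established at eligibility. Pre-specified adjustment could add about 0 to 6 points of power at 92 events, and would cost about half a point if none is prognostic. The upper end needs all the covariates to be strong together. With moderate effects the gain is about 1 to 3 points.

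The range rests on assumed prognostic strengths and prevalences, an assumed two-sided alpha of 0.05 and a single analysis. The stronger conclusion, that the trial is underpowered or wrongly analysed for lack of adjustment, does not follow: the plain log-rank reproduces the design's own figures.

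**What to change.** **If no comparative data have been seen** (before the 46-event look, if it has not occurred): amend the Primary endpoint section so that the primary test is either
- a covariate-adjusted log-rank, which keeps the marginal hypothesis the design was sized on, or
- the treatment effect from a Cox model.

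Name the covariates: GTV largest dimension (continuous), unresected vs R2, and histology in three levels (adenoid cystic carcinoma, sarcoma, chordoma). Use the same test at both looks. Report the plain log-rank and the unadjusted hazard ratio alongside. Do not stratify on every covariate cell.

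**If the interim look has taken place:** keep the plain log-rank as primary and pre-specify the adjusted analysis as supportive. The article projected the look at 42 months after first inclusion, which is about June 2021 counting from December 2017 at the planned enrolment rate. It does not say whether the look has happened.

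**Cost:** a short amendment, with its timing relative to unblinded data documented because the trial is open-label. No new assessments should be needed, but confirm that the actual GTV dimension is recorded and not only that it met the limit. The statistical costs are a small power loss if the covariates are weak, slight small-sample inflation of type I error for the adjusted log-rank (which should be checked by simulation for the version chosen), and a conditional hazard ratio if Cox is used.
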